### Saliva cortisol

As a measure of HPA-axis activity, saliva cortisol will be collected using cotton dental rolls, including 4 sequential samples at 30-min intervals starting at awakening and 3 sequential samples at hourly intervals starting 2 h before predicted bedtime with the last sample at bedtime. The samples will be collected the following day and subsequently delivered to the laboratory, where they will be centrifuged and stored at −80 °C. Samples will be analysed using a cortisol assay on an immunoanalyser system. For determination of the diurnal time course of saliva cortisol levels, only days with at least 6 valid samples will be included in analyses.

### Hair cortisol

Hair cortisol will be assessed as a validated biomarker for long-term cortisol exposure. The maternal hair strands will be collected and processed according to existing methods [65]. With this method, cortisol levels can be retrospectively assessed depending on hair length (i.e. one month for each centimetre of hair). Norm data from healthy pregnant controls will be available through one of our other ongoing studies.

### Saliva melatonin

As a measure of a participant’s circadian phase position, saliva melatonin levels will be collected using cotton dental rolls at hourly intervals with 3 sequential samples, starting 2 h before predicted bedtime with the last sample at bedtime, under dim light conditions. One sample will be taken at awakening. The samples will be collected the following day and subsequently delivered to the laboratory, where they will be centrifuged and stored at −80 °C. All samples will be analysed using Liquid Chromatography Tandem Mass Spectrometry (LC-MS/MS). For determination of a rise in melatonin levels in het evening, only days with 3 valid evening samples will be included in the analyses [23].

The Dim Light Melatonin Onset (DLMO; the time point when melatonin secretion rises over a predefined threshold in the evening [66]) will be calculated after measuring the melatonin evening curve. The DLMO is a reliable estimate of circadian phase position [66].

#### Secondary outcome measures (circadian rhythm)

The circadian rhythm during pregnancy will be studied through actiwatches and the PSQI.

### Actigraphy

Actigraphy, the continuous assessment of activity with a watch-sized non-dominant wrist-worn recorder (Actiwatch Spectrum, Philips Respironics, Pittsburgh, USA), is a validated technique to obtain estimates of sleep and rest-activity rhythms [23, 67, 68]. Sleep analyses software (Actiware 6.0, Philips Respironics, Pittsburgh, USA) will be used to obtain estimates of sleep parameters. The software will calculate end and start of sleep. Further, assumed sleep (the difference between the end and the start of sleep), actual sleep time (amount of sleep determined by algorithm), sleep onset latency (the time between lights out and sleep onset) and sleep efficiency (the percentage of actual sleep time between sleep onset and final awakening, excluding sleep onset latency) will be calculated [23]. Rest-activity rhythms will be calculated, using different actimetric variables, such as interdaily stability and intradaily variability [23].

### PSQI

The PSQI, a structured 19-item self-questionnaire with 5 additional items reported by bedpartner, assesses sleep quality, including a wide variety of factors, such as sleep duration and latency [69]. The sum score ranges from 0 to 21 points, with higher values corresponding to lower sleep quality [69]. These 19 items generate 7 component scores: subjective sleep quality, sleep latency, sleep duration, habitual sleep efficiency, sleep disturbances, use of sleeping medication and daytime dysfunction [69].

A cut-off of 5 will be applied, where a score of <5 indicates poor sleep and ≥5 indicates good sleep [69]. The PSQI has a sensitivity of 89.6 % and a specificity of 86.5 % [69].

The PSQI will be assessed on a monthly base and weekly in the intervention period.

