## Methods/Design

### Hypotheses

Primary hypothesis: Daily treatment with 6 weeks of morning BLT improves depressive symptoms during pregnancy.

Secondary hypotheses:Clinical improvement of depressive symptoms is accompanied by improved sleep patterns, lower basal cortisol levels and normalized melatonin concentrations during pregnancy.Treatment with BLT during pregnancy improves birth and child outcomes: higher gestational age, higher birth weight, less regulation problems in infants and lower cortisol stress response. In addition, infants will show lower long-term cortisol exposure.

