### MABS

We ask mothers (and fathers, if available) to fill out the MABS, a questionnaire consisting of various subscales [70]. In this study, we use 3 subscales of the MABS: infant alertness-responsiveness, unsettled-irregular behaviour of the infant and lack of confidence in care-taking [70], resulting in a 36-item questionnaire.

The unsettled-irregular behaviour scale consists of 8 items (e.g. ‘After feeds, I’ve used rocking or cuddling to settle my baby), the alertness-responsiveness scale of 15 items (e.g. ‘My baby watches my face’) and the lack of confidence in feeding of 13 items (e.g. ‘I’ve felt clumsy in caring for my baby’). Parents are asked to score the various statements with a score between 0 (not at all) and 5 (very much/often), which results in a sum score of 0–180. The subscale sum scores range from 0 to 75 for infant unsettled-irregular behaviour, from 0 to 40 for infant alertness-responsiveness and from 0 to 65 for lack of confidence in care-taking [70]. A higher score on the infant unsettled-irregular behaviour scale correlates to more irregular behaviour, whereas a higher score on the infant alertness-responsiveness scale points to more alert behaviour [71]. A higher score on the lack of confidence scale suggests that the mother is less confident in taking care of the baby. Reliability of the MABS ranges from 0.81 to 0.93 (Cronbach’s α), depending on the used subscale [70].

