#### Secondary outcomes

For saliva cortisol, areas under the curves for the morning and evening (i.e. 7 to 9 AM and 8 to 11 PM) will be calculated for subsequent analyses [23]. For saliva melatonin, areas under the curves for the evening (i.e. 8 to 11 PM) will be calculated for subsequent analyses [23].

Continuous outcomes, e.g. saliva cortisol and melatonin, will be tested with the unpaired t-test and linear mixed model. Categorical outcomes, e.g. sleep quality, will be tested with Chi-Square Test and generalized linear mixed model.

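### The PSQI good/poor sleep labels contradict the scale's stated direction, so the binary sleep outcome would be reported the wrong way round if coded as written; two MABS subscale ranges need a minor correction

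*Protocol article*

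**What the plan says.** **PSQI.** The PSQI section of the protocol article gives the scale's range and direction: "The sum score ranges from 0 to 21 points, with higher values corresponding to lower sleep quality". The next paragraph sets the classification rule: "A cut-off of 5 will be applied, where a score of <5 indicates poor sleep and ≥5 indicates good sleep". Table 1 schedules the questionnaire at baseline, weekly during the intervention, and at T1, T2, T3 and T5.

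**Where the classification is used.** Under Statistical analysis, Secondary outcomes, the article states: "Categorical outcomes, e.g. sleep quality, will be tested with Chi-Square Test and generalized linear mixed model". The first of the secondary hypotheses gives the expected direction: "Clinical improvement of depressive symptoms is accompanied by improved sleep patterns".

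**MABS.** Each item is scored from 0 to 5. On item counts the article says "The unsettled-irregular behaviour scale consists of 8 items" and gives "the alertness-responsiveness scale of 15 items"; a third subscale has 13. On ranges it says "The subscale sum scores range from 0 to 75 for infant unsettled-irregular behaviour, from 0 to 40 for infant alertness-responsiveness", with 0 to 65 for the third subscale and 0 to 180 for the total. The third subscale is about lack of confidence, described in one place as confidence in care-taking and in another as confidence in feeding.

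**The concern.** The PSQI rule is a definite instruction about how a score becomes a category, and it runs against the direction given just before it. Improved sleep belongs to a secondary hypothesis and to the second aim. If the binary variable is built from the printed labels, women moving from high to low scores, which the article itself describes as better sleep, would be counted as moving from good sleep to poor. A benefit of bright light would then be tabulated as a harm, or the reverse. The test output would give no warning, because a two-sided test does not depend on which category is called good.

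The MABS paragraph has a lesser problem: two of its three printed ranges cannot be obtained from the item counts printed beside them. Anyone using the article to set range checks or to interpret subscale scores has two incompatible descriptions.

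**Working it through.** **PSQI, direction against labels.** Inputs: the range and direction, and the cut-off rule, both from the PSQI section.

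| Score | Sleep according to the stated direction | Printed label |
|---|---|---|
| 0 to 4 | best end of the scale | poor |
| 5 to 21 | worse end of the scale | good |

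Both rows disagree. At the printed cut-off, every score receives the label opposite to the one its direction implies. Aligning the labels with the direction gives good sleep for low scores and poor sleep for high scores. The text alone cannot settle which side a score of exactly 5 belongs on.

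**What the swap does to a result.** The article gives no expected sleep proportions, so the counts here are assumed purely for illustration: 63 women per arm (the per-arm figure in the Sample size section), with 38 of 63 on bright light and 25 of 63 on dim red light scoring below 5.

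- Labels aligned with the direction (below 5 is good): difference in good sleep = 38/63 - 25/63 = 13/63 = +20.6 percentage points. Odds ratio = (38 × 38)/(25 × 25) = 1444/625 = 2.31.
- Labels as printed (5 or more is good): difference = 25/63 - 38/63 = -20.6 percentage points. Odds ratio = 625/1444 = 0.43.
- Chi-square without continuity correction, either way: 126 × (1444 - 625)² / 63⁴ = 5.37, p = 0.021.

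The same holds for a generalized linear mixed model with a logit link: exchanging the two categories changes the sign of the coefficients and leaves their standard errors and two-sided p-values as they were.

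**MABS, maximum = items × 5.** Inputs: item counts, item scoring and ranges from the MABS section.

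| Subscale | Items | Items × 5 | Printed maximum | Items implied by the printed maximum |
|---|---|---|---|---|
| Unsettled-irregular | 8 | 40 | 75 | 75/5 = 15 |
| Alertness-responsiveness | 15 | 75 | 40 | 40/5 = 8 |
| Lack of confidence | 13 | 65 | 65 | 65/5 = 13 |
| Total | 36 | 180 | 180 | 36 |

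The third subscale and the total reproduce. The two mismatches are exact mirror images, so either the counts or the ranges have been exchanged. The total cannot reveal this, since 40 + 75 and 75 + 40 are both 115.

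**The case against.** The strongest reply is that this is a drafting slip that exposes itself. The correct direction stands in the same short section, so whoever codes the variable will meet both statements and probably notice. That is a fair reason to keep the severity modest. It does not remove the point: the rule is worded as the one that will be applied, and readers will compare the published result with it.

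Second, the statistical section mentions sleep quality without naming the PSQI cut-off, and the PSQI also has a component called subjective sleep quality. The Outcome measures section does not list a good/poor sleeper outcome. The link to the dichotomy is therefore the most plausible reading rather than an explicit statement. This qualification stands.

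Third, a reader might go further and infer that the trial throws away information by dichotomising a 0 to 21 score, and so should be told to make the continuous score the main PSQI analysis. The article does not support that. Its General and Secondary outcomes paragraphs already assign repeatedly measured continuous variables to linear mixed models. Nothing says the binary version replaces the score, and any figure for information lost would need a distribution and a split that the article does not give.

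Fourth, a reader might infer that the MABS mismatch means items will be assigned to the wrong subscale. This is not shown either. The article names the subscales, gives an example item for each, states their directions and cites the instrument. Subscale scores come from summing items, and no planned analysis uses the printed maxima.

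**Conclusion.** The PSQI labels are wrong as written, judged only against the article's own statement of direction. The consequence is conditional. If the labels are coded literally, and if the categorical sleep-quality outcome is this dichotomy, that secondary result is reported with its direction reversed at an unchanged p-value. The 20.6-point figure only illustrates the mechanism and does not predict the size of any effect. The continuous PSQI score, the actigraphy measures, the primary depression outcomes and the sample size are untouched, so this is a small but certain correction to a secondary outcome and does not threaten the trial's main conclusion.

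The MABS discrepancy is real and arithmetically exact, but it is a minor erratum. The article shows that the counts and ranges of two subscales are exchanged relative to each other. It does not show which pair is wrong, so it should not be read as proof that the ranges are the faulty side.

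**What to change.** In the PSQI section, swap the labels so that low scores indicate good sleep and high scores poor sleep. Check against the instrument whether a score of exactly 5 counts as good or poor, and make the scoring syntax match. One added phrase in the Secondary outcomes paragraph, stating whether the categorical sleep-quality outcome is this PSQI dichotomy, would remove the remaining ambiguity.

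In the MABS section, reconcile the item counts and ranges of the unsettled-irregular and alertness-responsiveness subscales with the instrument, and use one name for the lack-of-confidence subscale.

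The cost is two corrected paragraphs, a clarifying phrase and a check of the scoring syntax. Data collection, visits and sample size do not change.

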#### Secondary outcome measures (infant)

As infant outcome measures, birth outcomes, infant stress response, infant long-term cortisol exposure and behaviour will be studied.

### Birth outcomes

After birth (T4), information will be obtained regarding complications during delivery and childbirth from the medical records: hypertension, pre-eclampsia, delivery aspects (duration, start with or without induction, augmentation, method of pain relief if any, instrumental delivery, caesarean section, hospital admission) and first week complications after delivery.

### Infant stress response

To measure the infant stress response, we will collect saliva cortisol before and 15, 30 and 45 min after a routine vaccination at T5. We will use the same procedures and analyses as with the mothers.

### Infant long-term cortisol exposure

To measure the long-term cortisol (intra-uterine) exposure, we will collect hair samples of the infant at T5. We will use the same procedures and analyses as with the mothers.

### Infant behaviour

To study infant behaviour, we will assess the questionnaires Mother and Baby Scales (MABS) and Child Behaviour Checklist (CBCL).

### MABS

We ask mothers (and fathers, if available) to fill out the MABS, a questionnaire consisting of various subscales [70]. In this study, we use 3 subscales of the MABS: infant alertness-responsiveness, unsettled-irregular behaviour of the infant and lack of confidence in care-taking [70], resulting in a 36-item questionnaire.

The unsettled-irregular behaviour scale consists of 8 items (e.g. ‘After feeds, I’ve used rocking or cuddling to settle my baby), the alertness-responsiveness scale of 15 items (e.g. ‘My baby watches my face’) and the lack of confidence in feeding of 13 items (e.g. ‘I’ve felt clumsy in caring for my baby’). Parents are asked to score the various statements with a score between 0 (not at all) and 5 (very much/often), which results in a sum score of 0–180. The subscale sum scores range from 0 to 75 for infant unsettled-irregular behaviour, from 0 to 40 for infant alertness-responsiveness and from 0 to 65 for lack of confidence in care-taking [70]. A higher score on the infant unsettled-irregular behaviour scale correlates to more irregular behaviour, whereas a higher score on the infant alertness-responsiveness scale points to more alert behaviour [71]. A higher score on the lack of confidence scale suggests that the mother is less confident in taking care of the baby. Reliability of the MABS ranges from 0.81 to 0.93 (Cronbach’s α), depending on the used subscale [70].

### CBCL

We ask mothers (and fathers, if available) to fill out the CBCL/1.5–5, a diagnostic 99-item questionnaire which quantifies skills and behavioural problems. The questionnaire consists of different scales: emotionally reactive, anxious/depressed, somatic complaints, withdrawn, sleep problems (Internalizing Problems), attention problems and aggressive behaviour (Externalizing Problems) [72]. Together, the Externalizing and Internalizing Problems form the Total Problems [72]. Items can be scored with 0 (not at all), 1 (a little or sometimes) or 2 (clearly or often), resulting in different sum scores for the different scales. Norms for these scales were constructed, using a large representative sample of children [72].

Reliability of the CBCL is 0.85 [73].

#### Chronotype

The participant’s chronotype will be verified at screening, since evening types are found to be more prone to depression than morning types [74, 75]. In this study, this will be assessed with the Munich Chronotype Questionnaire (MCTQ), a structured 19-item self-report measure of an individual’s chronotype, based on sleep times, self-reported light exposure and self-assessed chronotype (extreme, moderate or slight early, normal or slight, moderate or extreme late), taking rest and working days in consideration [76]. The participant can be classified to 1 of the 7 chronotypes by utilizing data on the participant’s midsleep phase and sleep debt [76]. Sum score ranges from 16 to 86, with the lowest score indicating extreme late chronotypes. The MCTQ correlates well with the Horne-Östberg Morningness-Eveningness Questionnaire – especially the MCTQ-assessment of time of midsleep (*r* = −0.73 on free days and *r* = −0.61 on workdays) [77].

### Statistical analysis

#### General

Data will be analysed using SPSS 21.0. For treatment effect analyses, we will apply an intention-to-treat procedure, since none of the participants will switch to another condition and we will include all observations of all participants until study end or withdrawal.

If necessary, skewed continuous variables will be transformed to normality prior to the analyses.

For the continuous variables and categorical variables that are assessed more than twice, we will deploy linear mixed models and generalized linear mixed models respectively. These models use all available data and account for within-subject correlation over time. They can also be used to adequately deal with possible baseline imbalances. Variables measured only once will be compared between the randomized groups using the unpaired t-test, or the Chi-Square test in case of categorical variables. All effect parameters will be supplied with a 95 % confidence interval.

Primary outcome analysis will be first crude, than adjusted. If despite randomization, prognostically important factors differ between the groups, they will be adjusted for supplemental analyses.

#### Primary outcomes

Changes in HAM-D and EPDS rating scale scores over time will be analysed using generalized linear mixed models. Differences from baseline of HAM-D and EPDS scores at every time point will be the dependent variables, time will be the within-subject factor and treatment (BLT versus DRLT) will be the between-subjects factor.

Additional analysis will use alternative definitions of change: instead of the numerical difference of scores before and after, we will use a dichotomous response variable where improvement of ≥ 50 % to a final score ≤ 8 on HAM-D and ≤ 5 on EPDS is defined as success, otherwise not. Finally, we will perform sensitivity analysis to examine robustness of the findings with other methods using data imputation (last observation carried forward multiple imputation).

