### BLT and depression during pregnancy

The SCN generates the circadian rhythms in physiology and behaviour, including reproductive hormones. Pregnant women typically show disturbed, desynchronised circadian rhythms, resulting in disturbed sleep patterns, which puts them at risk for depression [39]. Moreover, disturbed sleep and decreased physical condition put pregnant women at risk for decreased activity and less exposure to daylight [40], which might further enhance their risk for depression.

Two small (*n* = 10 and *n* = 27) randomized controlled trials among pregnant women with non-seasonal depression showed significant improvement of depression among women exposed to BLT compared to placebo [41, 42]. Treatment effect in terms of mean improvement of depressive symptoms was comparable with the effects of antidepressant medication (effect size around 0.45), making it a competitive treatment for antepartum depression, but without the possible adverse effects of medication to the unborn child. Although these studies provide evidence for the effectiveness of BLT for depression during pregnancy, their sample size is small.

While in previous studies among elderly patients cortisol and melatonin rhythms normalized after BLT treatment [23], the question is whether improvement of depressive symptoms after BLT in pregnant women is also mediated through improved endocrine functioning or whether these symptoms are primarily determined by the physiology of pregnancy itself. Therefore, we will also examine the circadian rhythms and hormone levels of the pregnant women, to study whether BLT also effects endocrine functioning during pregnancy.

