### Outcome measures

The primary outcome measure will be the average change in depressive symptoms between the two groups, as measured by the Structured Interview Guide for the Hamilton Depression Scale – Seasonal Affective Disorder version (SIGH-SAD) and the EPDS at different time points. Second, we will study responders vs. non-responders, where response is defined as a ≥50 % decrease to a final score of ≤ 8 on the 17-item Hamilton scale and ≤ 5 on the EPDS.

The secondary outcome measures of this study will be the changes in maternal cortisol and melatonin levels (1), in maternal circadian rhythm (2) and in birth and child outcomes (3).Morning and evening cortisol levels in saliva will be measured as a measure for HPA-axis activity. Morning and evening melatonin levels in saliva will be measured as measure of a participant’s circadian phase position. Outcome measures will be the changes in cortisol and melatonin saliva levels between the two groups.Total 24-h cortisol excretion will be determined from urine. Outcome measure will be the changes in cortisol levels within and between the two groups.Hair will be used as a long-term measure for cortisol excretion. Changes in levels between the two groups will be used as outcome measure.Through actiwatches and a structured questionnaire (the Pittsburgh Sleep Quality Index – PSQI), information will be obtained regarding total sleep time, sleep efficiency and sleep onset latency, as well as circadian estimates from the rest activity rhythm such as intradaily and interdaily variability and rhythm amplitude.Differences in birth and child outcomes between the two groups will be used as outcome measures: pregnancy duration, birth weight, child behaviour, long-term cortisol exposure and cortisol stress response at a routine vaccination.

Finally, we will ask about user expectations and user experiences.

Complete follow-up will be pursued. In case of discontinuing or deviating from the intervention, we will collect outcomes of EPDS and SIGH-SAD assessment.

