### Sample size

Based on previous literature [23, 41, 56], we expect a small to moderate response (time x treatment interaction on depressive symptoms). This corresponds to a 10 to 15 % reduction of depressive symptoms over the full course of treatment. To demonstrate this (with an α of 0.05 and a β of 0.80), we will need a sample size of 63 participants per arm (126 in total). To account for lost to follow up during and after treatment, we will aim at including 150 participants. Power calculations were performed using GLIMMPSE 2.1.5 software [57].

In case of withdrawal of a participant during the recruitment period, another participant will be recruited to obtain the aimed number of participants.

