### SIGH-SAD

The SIGH-SAD is a 29-item structured interview and consists of 21 HAM-D (Hamilton Rating Scale for Depression) items and 8 atypical items, of which 11 items can be scored with a value of 0–2, 5 items with a value of 0–3 and 13 items with a value of 0–4 [61]. The sum score ranges from 0 to 63 for the HAM-D items and from 0 to 26 for the atypical items, resulting in a total sum score of 0 to 89 [61].

We will choose the original 17-item HAM-D questionnaire as primary measure, since it is more commonly used in clinical practice and research. Interrater reliability for the 17-item HAM-D questionnaire ranges from 0.82 to 0.98 [62]. Sensitivity and specificity are respectively 0.76 and 0.91 [62]. Positive and negative predictive value are respectively 0.77 and 0.92 [62]. Next to the original 17-item HAM-D questionnaire, we will use the entire SIGH-SAD questionnaire, since this questionnaire is the current benchmark for assessment of severity of depression in light therapy trials.

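### The primary question is stated in several unreconciled ways, so the contrast that was powered cannot be identified in the primary analysis, and HAM-D and EPDS share one alpha with no stated rule

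*Protocol article*

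**What the plan says.** The protocol article describes the primary question in five places:

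- **Hypotheses:** "Daily treatment with 6 weeks of morning BLT improves depressive symptoms during pregnancy". The opening of the primary outcome measures under Measurements has the same limit to pregnancy.
- **Outcome measures:** "The primary outcome measure will be the average change in depressive symptoms between the two groups", on SIGH-SAD and EPDS at unspecified time points. The abstract also names these two instruments.
- **Sample size:** "we expect a small to moderate response (time x treatment interaction on depressive symptoms", with the window given by "This corresponds to a 10 to 15 % reduction of depressive symptoms over the full course of treatment". The scale is not named. The error rates are "with an α of 0.05 and a β of 0.80"; I read the second figure as power.
- **SIGH-SAD:** "We will choose the original 17-item HAM-D questionnaire as primary measure", with the full SIGH-SAD used alongside it.
- **Statistical analysis, Primary outcomes:** "Differences from baseline of HAM-D and EPDS scores at every time point will be the dependent variables, time will be the within-subject factor", with treatment as the between-subjects factor.

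Table 1 schedules both instruments weekly during the intervention and at T1, T2, T3, T5, T6 and T7. T7 is 18 months postpartum.

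**The concern.** Three things differ between these places: the window (treatment course, pregnancy, or everything to 18 months postpartum), the quantity tested (interaction, average change, or change at each visit) and the scale. The analysis section does not say whether the primary test is the treatment main effect, the interaction or a contrast at one visit.

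The move to change scores adds a technical problem. When baseline is one of the time levels, a time-by-treatment interaction tests differential change, which is the treatment effect. When the outcome is already the difference from baseline, the interaction asks only whether the effect varies among post-baseline visits. A benefit that appears early and persists then leaves nothing for it to detect. The article itself says, under Intervention and in the Discussion, that BLT may work within a week.

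At stake is what the trial may claim. The same data could succeed or fail depending on a term, window and scale that the article leaves open.

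**Working it through.** **1. The plan's own figure.** The stated 63 per arm cannot be rerun as an interaction, because the SD, within-subject correlation, number of measurements and scale are not given. A plain two-sample comparison at one time, two-sided 0.05 and 80% power, gives n = 2(1.960 + 0.842)²/d². At d = 0.50 this is 62.8, so 63 per arm. The match is suggestive only; the article does not say that this was the calculation. The Background mentions an "effect size around 0.45", for which the formula gives about 78 per arm and 71% power at 63.

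**2. Visits.** Weeks 1–5, T1, T2, T3, T5, T6 and T7 make 11 post-baseline visits: eight in pregnancy and three postpartum.

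**3. Assumptions for the comparison.** 63 per arm (from the article); d = 0.50 in SD units of the change score, exchangeable correlation 0.5 between visits and two-sided 0.05 (all assumed).

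- Average over k visits: SE = √[(2/63)(1 + (k−1)·0.5)/k]. This is 0.1316 for k = 11, 0.1336 for k = 8 and 0.1782 for a single visit.
- Interaction on change scores: chi-square on 10 df, noncentrality 63/(2(1−0.5)) × Σ(d_j − mean d)² = 63 × Σ(d_j − mean d)².

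**4. Constant benefit of 0.50 from week 1.** The squared deviations sum to zero, so the interaction has power equal to its size.

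**5. Benefit that fades.** It rises linearly to 0.50 at week 6, is 0.50 at T2, 0.40 at T3 and zero at T5–T7. The eight pregnancy values sum to 2.65.

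- Mean over 11 visits: 2.65/11 = 0.241; 0.241/0.1316 = 1.83.
- Mean over the 8 pregnancy visits: 2.65/8 = 0.331; 0.331/0.1336 = 2.48.
- T1: 0.50/0.1782 = 2.81.
- Interaction: Σ(d_j − mean d)² = 1.0419 − 11 × 0.2409² = 0.4035; noncentrality 63 × 0.4035 = 25.4.

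| Term tested | Constant benefit | Benefit absent postpartum |
|---|---|---|
| Interaction on change scores, 10 df | 5% | 96% |
| Main effect, all 11 visits | 97% | 45% |
| Average, 8 pregnancy visits | 96% | 70% |
| Contrast at T1 | 80% | 80% |

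**6. Two scales, each at 0.05, either sufficient.** Independent scales: 1 − 0.95² = 9.75%. Correlated scales (assumed): 9.1% at 0.5, 8.3% at 0.7 and 7.8% at 0.8. Splitting alpha to 0.025 each at d = 0.50 needs 77 per arm (154 in total) before dropout; at 63 per arm the power is 71%.

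**The case against.** The strongest reply is that the analysis section names no tested term. Joining the interaction from the sample size section to the change-score outcome of the analysis section makes a hybrid that no sentence states. The powered interaction may include baseline, and the mixed model may contain the intended contrast. **This stands.** A reader might infer that the powered hypothesis is not the one analysed; the text shows only that it cannot be identified there. Nor is the model weak in itself: in each scenario above, one of its terms has higher power than the T1 contrast. The difficulty is that it is a different term each time, and none is chosen in advance.

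Second, the primary question is twice limited to pregnancy, and the Covariates section treats the period after pregnancy with extra adjustment, which hints at a separate postpartum analysis. **This stands in part.** It makes dilution less certain, but the analysis under Primary outcomes still takes every time point.

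Third, a reader might count three primary scales or conclude that alpha is uncontrolled. The article does not support either. It prefers HAM-D-17 to the full SIGH-SAD, and the primary analysis uses only HAM-D and EPDS. Nothing says that success on either scale is enough; if both were required, type I error would not exceed 5%. The analysis plan is not shown and may hold a rule. What remains is that two scales sit under the primary heading with one alpha of 0.05 and no ranking here.

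**Conclusion.** The point holds as a failure to reconcile, not as a proven mismatch. The window, tested quantity and scale differ between sections that should agree, and the powered contrast cannot be found in the primary analysis. This is more than detail left to an analysis plan: a plan that picked one version would contradict another part of the protocol.

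On the assumed inputs, power for the same true effect ranges from 5% to about 97% for a constant benefit and from about 45% to 96% for one absent postpartum, depending on the term chosen. The type I error of about 8–10% applies only if success on either scale suffices. The power figures depend on d = 0.50, correlation 0.5 and the effect profiles, none of which the article supplies. They show that the choice matters; they do not predict the trial's power.

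**What to change.** Name one primary scale, one window and one test. The choice that fits the existing text best is HAM-D-17, already called the primary measure, at T1, the end of treatment, as a single-degree-of-freedom BLT minus DRLT contrast from the repeated-measures model. An average over pregnancy visits would also fit the hypothesis, if it is stated in advance and powered as such.

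Make EPDS in the same window the key secondary outcome, tested only if HAM-D-17 succeeds, or state that both scales must succeed. Report the full SIGH-SAD, the remaining visits and postpartum visits T5–T7 as secondary, with estimates and 95% confidence intervals. Bring the abstract, Outcome measures, Sample size and Primary outcomes into line. In the power statement, give the scale, SD, correlation, visits and contrast used.

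The cost is wording. With one scale and one visit, 63 per arm stands if d = 0.50 is accepted; requiring both scales would need its own power calculation. The drawback is that EPDS and postpartum results can no longer carry the primary claim alone.
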